#### 2.7.2. Secondary Outcomes

The secondary outcomes of this study include the early interruption rate; the withdrawal period (including the early interruption rate due to AEs of CTCAE grade 3 or above); the incidence of adverse drug reactions (ADRs, including irAEs for atezolizumab monotherapy and combined therapy [30,32,33] at CTCAE grade 3 or above with an incidence rate of over 1%); fatigue symptom improvement using the Functional Assessment of Chronic Illness Therapy—Fatigue domain (FACIT-F; Trial Outcome Index (TOI)—Fatigue) [34], the European Organization for the Research and Treatment of Cancer Quality of Life Questionnaire (EORTC-QLQ-C30) fatigue subscale [35,36,37], and the numeric rating scale (NRS) for fatigue; evaluations of skeletal muscle loss (using the strength, assistance with walking, rising from a chair, climbing stairs, and falls (SARC-F) questionnaire [38], a body composition test, the sit-to-stand test, and the thoracic muscle index), changes in the ECOG PS, pattern identification diagnosis, and treatment compliance. Demographic information such as age, sex, medical history, and laboratory tests will also be recorded.

Early discontinuation will be defined as failure to complete the planned study administration protocol regardless of the cause or dosing regimen, except when discontinuation is due to progressive disease. In addition, even if the planned three-cycle schedule has been completed, if the actual number of ICI doses during the treatment period is less than 60% of the total planned number due to toxicity, these patients will be included in the category of early discontinuation. To investigate therapeutic effects based on pattern identification, the cold–heat pattern identification questionnaire will be used to differentiate cold, non-cold, heat, and non-heat type classifications. This questionnaire consists of a five-point scale with 15 questions evaluating cold and heat types [39,40].

#### 2.7.3. Exploratory Outcomes

The exploratory outcomes for this study are the ORR (defined as the proportion of patients with the best overall complete or partial response) of atezolizumab treatment according to the RECIST version 1.1 guidelines and immune profiles.

Blood samples (approximately 12 mL) will be collected for immune profiling analysis at the time points of pre-treatment and after treatment of 3 cycles (EOT). Additionally, sample collection at first cycle treatment will proceed according to the investigator’s judgement. Basic immune cell subtypes, fractions of Th1/Th2/Th17, Treg subtypes, naïve/memory/senescence markers, and the expression of immune checkpoint receptors will be measured through a multicolor fluorescence-activated cell sorting analysis of peripheral blood mononuclear cell (PBMC) samples. Cytokine levels will be measured using a multiplex assay. Additionally, Th1, Th2, and Th17 cell fractions and natural killer cell activity will be measured. Moreover, a total transcriptome analysis of PBMCs will be performed via sequencing.

#### 2.7.4. Safety Outcomes

At each visit, all adverse reactions reported by the participant and observed by the investigator will be recorded, including those pertaining to vital signs and blood tests. All AEs (including irAEs) and ADRs related to ICI treatment in NSCLC patients will be descriptively recorded with detailed explanations, including information about the seriousness, severity, and causality of the events. Safety and tolerability will be assessed according to the National Cancer Institute Common Terminology Criteria (CTCAE v4.03). If possible, AEs collected during the trial period will be recorded using Medical Dictionary for Regulatory Activities (MedDRA) terms through a case report form.

### 2.8. Sample Size

To our knowledge, this is the first exploratory clinical trial to investigate the improvement in symptoms and AEs following BJIKT treatment as compared to placebo in patients with advanced NSCLC who are being treated with ICIs.

Considering the exploratory nature of the clinical trial and the number of patients available from each center, a total of 30 participants (15 in each group) will be enrolled. Recruitment started on 25 March 2022 and is expected to be completed by 30 June 2023.

### 2.9. Statistical Analysis

All statistical analyses will be performed using a two-tailed test with a 5% level of significance. An independent statistician will conduct statistical analysis using SAS^®^ Version 9.4 (SAS Institute Inc., Cary, NC, USA). 

The primary efficacy variable will be summarized using the full analysis set (FAS), and the per-protocol set (PPS) will be used for a supportive analysis. All other efficacy analyses will be based on the FAS. Safety variables will be summarized using a safety set (SS), which includes all participants receiving at least one dose of the study medication. The FAS will consist of all randomized participants who received at least one dose of the study medication and who underwent a valid measurement of the primary efficacy variable at baseline.

The PPS will consist of all participants in the FAS who showed no important protocol deviation affecting the primary efficacy variable.

Participants showing important protocol deviations will be predefined and evaluated during a data evaluation meeting prior to unblinding the data.

Categorical data will be presented as frequencies and percentages, and continuous data will be presented as means and 95% confidence intervals. 

The normality of continuous variables in the clinical data will be tested using the Kolmogorov–Smirnov test. Continuous data will be analyzed using the independent t-test or Wilcoxon rank-sum test, and categorical data will be analyzed using the chi-squared test or Fisher’s exact test for comparison of two groups. Mixed-effect model repeated measures (MMRM) will be used, with each group and visit time as fixed factors and subjects as random factors. Paired *t*-tests or Wilcoxon signed rank tests will be used to compare the factors before and after treatment. 

Pearson’s correlation or Spearman’s rank correlation tests will be used for each administration group in order to examine the correlations among various immune indicators measured in blood samples, treatment responses, and each identified pattern. The data collected in this study will be used as is for analysis without replacing or imputing missing values. 

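### Marker correlations are fixed separately within arms of at most 15 at a two-sided 5% level, which loses precision and gives no test of whether a correlation differs between arms

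*Protocol article*

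**What the plan says.** Section 2.9 (Statistical Analysis) sets one rule for everything: "All statistical analyses will be performed using a two-tailed test with a 5% level of significance". For the biomarker work it names Pearson or Spearman tests that "will be used for each administration group in order to examine the correlations among various immune indicators measured in blood samples, treatment responses" and identified patterns. Missing values are not imputed, so the number per arm can fall below the enrolled number.

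Section 2.8 gives that number: "a total of 30 participants (15 in each group) will be enrolled". It rests on feasibility ("Considering the exploratory nature of the clinical trial and the number of patients available from each center"), with no power statement.

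Section 2.7.3 describes a broad panel: cell subsets, T-helper and regulatory fractions, checkpoint receptors, natural killer activity, and cytokines ("Cytokine levels will be measured using a multiplex assay"). It adds that "a total transcriptome analysis of PBMCs will be performed via sequencing". ORR is "defined as the proportion of patients with the best overall complete or partial response". Both ORR and the immune profile are labelled exploratory. Table 1 schedules tumour evaluation at screening and at V3 only, so response rests on one scan after baseline.

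**The concern.** The by-arm split is a stated method, not a gap that an analysis plan would fill. It halves a sample that is already small. It also invites comparison of two p-values, one per arm, with no test of the difference between the two correlations. A marker significant under BJIKT but not under placebo would look like a BJIKT-specific signal even if the underlying relation were identical in both arms. The between-group tests and the repeated-measures model in section 2.9 compare levels of a variable, not the strength of a correlation.

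Immune status and ORR together form the third aim in the Introduction, and the Conclusions offer the findings as a basis for further integrative research. Arm-discordant or chance signals could misdirect that work. The trial's primary safety outcome is not affected.

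**Working it through.** The article gives no power, expected ORR, marker count or gene count for this part, so there is no figure to reproduce.

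**Inputs from the article:** two-sided 0.05 (2.9); 15 per arm, 30 in total (2.8); correlations by arm (2.9); ORR as CR/PR (2.7.3).

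**Assumed:** true correlations of 0.3, 0.5 and 0.7; ORR from 5% to 30%; 10 to 100 panel markers; 10,000 to 20,000 genes.

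**1. Precision.** The interval is tanh(atanh(r) ± 1.96/√(n−3)), with atanh(0.5) = 0.549.
- n = 15: 0.549 ± 1.96/√12 = 0.549 ± 0.566, giving -0.02 to 0.81.
- n = 30: 0.549 ± 1.96/√27 = 0.549 ± 0.377, giving 0.17 to 0.73.
- Both arms combined after stratifying by arm (12 + 12 = 24 in place of 27): 0.549 ± 0.400, giving 0.15 to 0.74. Allowing for arm costs little.

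**2. Power and discordance.** Power ≈ Φ(atanh(ρ)·√(n−3) − 1.96). At n = 15 this is 0.187, 0.477 and 0.852 for ρ = 0.3, 0.5 and 0.7. With the same ρ in both independent arms, the chance that exactly one is significant is 2p(1−p):
- ρ = 0.3: 2 × 0.187 × 0.813 = 30%
- ρ = 0.5: 2 × 0.477 × 0.523 = 50%
- ρ = 0.7: 2 × 0.852 × 0.148 = 25%

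Pooling 30 patients at ρ = 0.5 gives Φ(0.549 × √27 − 1.96) = Φ(0.89) = 81%. Stratified by arm it is Φ(0.549 × √24 − 1.96) = Φ(0.73) = 77%.

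**3. What a direct test of difference can do.** The standard error of the difference in Fisher z is √(1/12 + 1/12) = 0.408, so the 95% half-width is 1.96 × 0.408 = 0.80 on that scale. This is imprecise, but it shows the reader how little is known.

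**4. Few responders, if response is binary.** With no responder in an arm, the correlation is undefined by any method. With one responder of 15, the smallest exact two-sided rank p is 2/15 = 0.13 (the t-approximation for Spearman gives 0.107). With two, it is 2/C(15,2) = 2/105 = 0.019, so 5% can be reached. Pearson with one responder can also reach 5%: in simulated null normal data it rejected 5.0% of the time. It then asks only whether one patient is an outlier.

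The chance of at most one responder is (1−π)^15 + 15π(1−π)^14, where π is the ORR, assumed equal in both arms:

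| Assumed ORR | One given arm | At least one of the two arms |
|---|---|---|
| 5% | 83% | 97% |
| 10% | 55% | 80% |
| 15% | 32% | 54% |
| 20% | 17% | 31% |
| 30% | 3.5% | 7% |

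For 30 pooled patients the chance of at most one responder is 18%, 5% and 1% at ORRs of 10%, 15% and 20%.

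**5. Number of tests.** Panel markers each correlated with response in both arms give 2 × k × 0.05 expected chance hits: 1 for 10 markers, 10 for 100. For 20 independent tests, the chance of at least one false hit is 1 − 0.95^20 = 64%. If genes were tested one by one at 5%, 10,000 to 20,000 genes would give 500 to 1,000 chance hits (0.05 × 10,000; 0.05 × 20,000).

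**The case against.** The strongest reply is that much of this belongs to an analysis plan that is not shown. The article does not say that tests are unadjusted. It gives no method or gene count for the transcriptome, and the correlation sentence does not mention it. A 5% level is even compatible with a 5% false discovery rate. A reader might infer that the whole transcriptome will be tested gene by gene with no correction and will yield hundreds of false hits; the documents do not establish that. This objection stands, and the gene figures are conditional only.

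A reader might also infer that a correlation with response cannot reach significance in this trial. That too goes further than the text. Section 2.9 speaks of treatment responses without saying that they enter as CR/PR or not, and ordered RECIST categories would suit Spearman. The barrier applies only to a binary response with no responder, or with one responder under a rank test, and its probability depends on an ORR that the article does not give.

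Third, the immune outcomes are already called exploratory ("The exploratory outcomes for this study are the ORR" and the immune profiles), the Discussion admits the small sample, and nothing in the article says that a one-arm finding will be claimed as a BJIKT effect. By-arm correlations are legitimate description in a pilot. BJIKT may shift end-of-treatment markers, so crude pooling could mislead, and an interaction term at 30 patients is imprecise. All of this is fair. It argues for allowing for arm when pooling and for keeping the by-arm results as description. It does not supply the missing test of a difference or recover the lost precision.

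**Conclusion.** The point holds for the by-arm correlations. Confining them to at most 15 patients roughly halves the information and leaves no way to judge whether arms differ. With an identical true correlation of 0.5, exactly one arm is significant about 50% of the time (30% at 0.3, 25% at 0.7). These figures assume complete data, approximately normal Fisher z values and independent arms; missing samples would make them worse.

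The sparse-responder problem is real but conditional on a binary response and on the ORR: 55%, 32% or 17% per arm at 10%, 15% or 20%. The false-discovery point is also conditional. It matters modestly for the panel, and greatly for the transcriptome only if that is tested gene by gene at a per-test 5%. This is a worthwhile, inexpensive improvement to an exploratory component.

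**What to change.** - Make the main correlation analysis a pooled one in all patients, stratified by or adjusted for arm.
- Base any claim of an arm difference on an arm-by-marker term, reported with its confidence interval and acknowledged as imprecise at 30 patients. Keep the by-arm correlations as description, with intervals.
- State how response enters the correlations. If it is CR/PR or not, report the number of responders per arm beside each result.
- Replace the per-test 5% level with Benjamini-Hochberg false discovery control (5% or 10%) for the multi-marker panel, and for the transcriptome if it is tested gene by gene.
- Optionally, add percent change in the target-lesion sum from screening to V3 as a further response measure. It is available only for patients with measurable disease, since inclusion criterion 7 also admits lesions that are only evaluable.

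The cost is some wording and a little more analysis, with no new patients, visits, samples or scans. The downside is fewer nominally significant markers.

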### 2.6. Interventions

The BJIKT will be prepared by Hanpoong Pharm & Foods Co., Ltd. (Iksan, Republic of Korea). It will be produced according to the Korean Good Manufacturing Practice guidelines outlined by Korea Ministry of Food and Drug Safety (MFDS) and manufactured so that there is no difference between them in shape, color, smell, or taste. A blinded pharmacist will check the storage, dispensation, and quality of the investigational products. 

The BJIKT used in this study will be a dried, light yellowish-brown to fine brown granule extracted with water. The extract is composed of 10 medicinal plants, as follows: *Ginseng Radix* 1.33 g, Atractylodis Rhizoma Alba 1.33 g, Astragali Radix 1.33 g, *Angelicae Gigantis Radix* 1.0 g, *Zizyphi Fructus* 0.67 g, *Bupleuri* root 0.67 g, *Citri Unshius Pericarpium* 0.67 g, *Cimicifugae Rhizoma* 0.33 g, *Zingiberis Rhizoma Recens* 0.17 g, and *Glycyrrhizae Radix et Rhizoma* 0.5 g (representing the dose for one day of treatment).

The placebo will be made of water-immersed crude extract, lactose hydrate, corn starch, hydroxypropyl cellulose, sucrose fatty acid ester, magnesium stearate, and light anhydrous silicic acid. Both drugs will be identical in appearance, shape, taste, and color (brown). The BJIKT and placebo granules will be sealed in opaque aluminum bags and will be administered to the participants in 4g doses. 

All enrolled participants will receive intravenous atezolizumab (1200 mg fixed dose) every three weeks on day 1 of each three-week cycle and will take BJIKT or placebo (4 g at a time) every day for approximately nine weeks regardless of withdrawal of the base drug, starting from the initiation of atezolizumab therapy. This regimen may be discontinued according to the investigator’s judgment. All participants will be requested to return the remaining drugs in order to calculate compliance. All medications and treatments that are clinically determined to be necessary for the patient can be prescribed. The investigators will record the details of concomitant medication and treatment information in the case report form during this clinical trial period (from the date of clinical trial registration to the end of observation for each subject).

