### 2.7. Outcome Measures

#### 2.7.1. Primary Outcomes

The primary study outcomes are the incidence of AEs, including irAEs and non- irAEs, and the incidence of AEs of CTCAE grade 4 or higher. These will be graded using the National Cancer Institute CTCAE v4.03 criteria [31].

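### Section 2.9 assigns 95% confidence intervals to continuous data only, so the two primary safety incidences have no planned interval, and at 15 per arm their p-values say little about safety

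*Protocol article*

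**What the plan says.** Section 2.7.1 makes safety primary: "The primary study outcomes are the incidence of AEs", covering immune-related and other events, together with "the incidence of AEs of CTCAE grade 4 or higher".

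Section 2.9 sets the format for each type of data: "Categorical data will be presented as frequencies and percentages, and continuous data will be presented as means and 95% confidence intervals". For group comparisons, "categorical data will be analyzed using the chi-squared test or Fisher’s exact test for comparison of two groups". The general rule is "All statistical analyses will be performed using a two-tailed test with a 5% level of significance".

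Section 2.8 sets the size: "a total of 30 participants (15 in each group) will be enrolled". The stated basis is "Considering the exploratory nature of the clinical trial and the number of patients available from each center". No power, precision target or safety margin is given.

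The Introduction lists the comparison of safety with placebo as the first aim.

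**The concern.** The format rule in section 2.9 gives an interval to one type of data and a different summary to the other. The primary outcomes are of the type that gets no interval. This is more than a detail left for a later document, because the article states a rule and the rule does not suit its own primary outcomes.

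A pilot of this size is useful for safety only if it shows how large an excess risk remains compatible with the data. Two percentages and a p-value do not show that. Whoever plans the next trial would have to work out the uncertainty from the counts.

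**Working it through.** **Inputs.** From the documents: 15 patients per arm (section 2.8), two-sided 5% level and a chi-squared or Fisher test (section 2.9), and a 27% rate of fatigue on atezolizumab monotherapy (Introduction). The article gives no rate for either primary outcome, so all event counts below are illustrative. Incidence is taken as the proportion of patients with at least one event.

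**The plan's own figure.** The 30 patients were set by feasibility, so there is no power or precision calculation to reproduce. Only 15 + 15 = 30 can be checked, and it agrees.

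**What the Fisher test needs at 15 against 15.** Enumerating all tables, two-sided p < 0.05 needs splits such as these:

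| Lower arm | Higher arm | Fisher p |
|---|---|---|
| 0/15 | 5/15 | 0.042 |
| 1/15 | 7/15 | 0.035 |
| 3/15 | 10/15 | 0.025 |
| 5/15 | 12/15 | 0.025 |

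Exact power, summing binomial probabilities over the rejecting tables, is 18% for 27% against 54%, a doubling of the fatigue rate. For an assumed 5% against 20% it is 8%. The 27% belongs to one symptom and not to a primary outcome, so it only gives a sense of scale.

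**Intervals for the risk difference.** The Newcombe method takes the Wilson limits (l, u) of each arm and combines them, with d = p1 - p2:

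- lower limit = d - √[(p1 - l1)² + (u2 - p2)²]
- upper limit = d + √[(u1 - p1)² + (p2 - l2)²]

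The Wilson limits are 0.109 to 0.520 for 4/15 (p = 0.267) and 0.248 to 0.699 for 7/15 (p = 0.467).

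- 4/15 against 4/15: d = 0. The half-width is √[(0.267 - 0.109)² + (0.520 - 0.267)²] = √(0.0249 + 0.0639) = 0.298. The interval is -30 to +30 points, with Fisher p = 1.0.
- 7/15 against 4/15: d = 0.200. Lower limit: 0.200 - √[(0.467 - 0.248)² + (0.520 - 0.267)²] = 0.200 - 0.334 = -0.134. Upper limit: 0.200 + √[(0.699 - 0.467)² + (0.267 - 0.109)²] = 0.200 + 0.281 = 0.481. The interval is -13 to +48 points, with Fisher p = 0.45.
- 4/15 against 0/15: d = 0.267 and the interval is +1 to +52 points, with Fisher p = 0.10. If these were grade 4 or higher events, the planned output would show a non-significant test beside a marked imbalance.

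**One arm with no events.** The Clopper-Pearson two-sided 95% upper limit is 1 - 0.025^(1/15) = 0.218, or 21.8%.

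**The case against.** The strongest reply is that this is a small exploratory pilot with no power target, so low power is expected. The sentence in section 2.9 can also be read as a general convention that does not forbid an interval for categorical data. Section 2.7.4 adds a descriptive record of each event's seriousness, severity and causality, and the Discussion names the small sample as a limitation and calls for larger trials to confirm safety.

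Much of this stands. Low power is not in itself a fault here, and an analysis plan that is not shown may add the interval. But an exploratory trial is meant to estimate, and estimates need their uncertainty. Event descriptions do not supply it, and a general caveat about sample size does not say how large an excess risk remains possible.

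Three stronger readings are tempting, and the documents do not support them:

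- **A non-significant result will be presented as evidence of safety.** No section sets such a rule or a margin, and the Discussion points the other way.
- **Unequal follow-up will bias the crude percentages.** The article is silent on exposure adjustment, which is commonly left to the analysis plan. The planned window is the same nine weeks or so for everyone, and section 2.6 has study drug taken "every day for approximately nine weeks regardless of withdrawal of the base drug". Observation can still end early, through death or withdrawal for example, but nothing indicates that it would differ between arms.
- **Toxicity of a later therapy will contaminate the outcome.** Section 2.6 requires concomitant treatment to be recorded and section 2.7.4 requires causality. Counting all events in the window by assigned group is a legitimate choice, and stopping the count at a new therapy would be a preference.

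**Conclusion.** The point holds in a limited form. Followed as written, section 2.9 gives the two primary safety outcomes counts, percentages and a two-sided 5% test, and reserves intervals for continuous data. At 15 per arm, equal results of 4/15 leave a risk difference anywhere from -30 to +30 points, and zero events in an arm leave a rate of up to 21.8%. The planned summary shows neither.

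The interval widths follow from the sample size and the illustrative counts, and other counts would change them. The gap in the reporting rule depends on no assumed rate. It is a reporting weakness that is cheap to correct, and it does not put the design or the conduct of the trial in doubt.

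**What to change.** Amend the sentence in section 2.9, and carry the change into the analysis plan, so that each primary outcome is reported with:

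- the count, percentage and exact (Clopper-Pearson) 95% interval in each arm;
- the between-group risk difference with a 95% interval, by either the Newcombe or the Miettinen-Nurminen method, chosen before unblinding.

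State that the safety interpretation rests on the interval for the difference and that the p-value is supportive. This matters because the two can disagree, as in the 4/15 against 0/15 example.

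The cost is a change of wording and a little extra analysis, with no new data or patients. The downside is that the intervals will be visibly wide.

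### As written, the MMRM's group term averages the arm difference over visits rather than giving the end-of-treatment difference, and no lead analysis is named for fatigue and muscle scores

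*Protocol article*

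**What the plan says.** Section 2.9 lists three kinds of analysis for continuous outcomes.

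- Between arms: "Continuous data will be analyzed using the independent t-test or Wilcoxon rank-sum test".
- Repeated measures: an MMRM "with each group and visit time as fixed factors and subjects as random factors". No treatment-by-visit term, baseline covariate or contrast visit is named. Nor does the section say whether the response is the raw score or the change, or whether the pre-treatment value counts as a visit.
- Before/after: paired t-tests, or "Wilcoxon signed rank tests will be used to compare the factors before and after treatment".

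It also states: "The normality of continuous variables in the clinical data will be tested using the Kolmogorov–Smirnov test". One significance statement covers everything: "All statistical analyses will be performed using a two-tailed test with a 5% level of significance". The three analyses are not ranked.

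Table 1 schedules the fatigue scales, SARC-F and the muscle test at screening, V1 (about week 3) and V3 (about week 9, marked as end of treatment). The body composition test differs: baseline, V1, V2 and V3. Section 2.7.2 makes all of these secondary outcomes. In Section 2.8, "a total of 30 participants (15 in each group) will be enrolled", chosen on grounds of exploratory purpose and patient availability.

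**The concern.** The Introduction states the aim for fatigue and muscle loss as improvement after treatment. The natural between-arm quantity is the difference at V3. A model with group and visit main effects assumes the same arm difference at every modelled visit and reports one number for all of them. If the benefit takes time to develop, that number is smaller than the V3 difference. If the screening value is entered as a response, the average also includes a time point where randomization makes the expected difference zero.

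Two further points add to this. A pre-treatment score that could sharpen the comparison is collected but not named as a covariate, which matters with 15 per arm. And with a two-sample test, an MMRM and before/after tests side by side, the article does not tell the reader which result will be the answer. The before/after tests carry no information on the difference between arms.

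**Working it through.** **The plan's own figure.** The sample size has no power calculation behind it ("Considering the exploratory nature of the clinical trial and the number of patients available from each center"). Only the allocation can be checked: 30/2 = 15 per arm, which is consistent.

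**Inputs from the article.** n = 15 per arm; two-sided 5%; the MMRM terms quoted above; visits from Table 1.

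**Assumed inputs, not in the article.** V3 difference d = 1 SD; equal correlation rho between visits (which a random subject effect implies), from 0.3 to 0.7; no missing data; several shapes of effect over time.

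**What the group term estimates.** With complete data it is the simple mean of the visit-specific differences.

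- Linear build-up (d/3 at V1, d at V3): with screening as a response, (0 + d/3 + d)/3 = 0.44 d; with V1 and V3 only, (d/3 + d)/2 = 0.67 d.
- Constant from V1: (0 + d + d)/3 = 0.67 d; V1 and V3 only, 1.00 d.
- Effect at V3 only: (0 + 0 + d)/3 = 0.33 d; V1 and V3 only, 0.50 d.

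**Standard errors, in SD units.**

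- Group term, three time points: sqrt[(2/15)(1 + 2 rho)/3]. At rho = 0.5 this is 0.298; a matrix least-squares calculation gives the same value.
- Group term, V1 and V3: sqrt[(2/15)(1 + rho)/2] = 0.316 at rho = 0.5.
- Two-sample test on raw V3: sqrt(2/15) = 0.365.
- Two-sample test on change: sqrt[(2/15) × 2(1 − rho)] = 0.365 at rho = 0.5.
- V3 adjusted for baseline: sqrt[(2/15)(1 − rho²)] = 0.316 at rho = 0.5.

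**Power at d = 1 SD** (noncentral t; 28 df, or 27 with baseline adjustment):

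| Analysis | Estimates | rho 0.3 | rho 0.5 | rho 0.7 |
|---|---|---|---|---|
| MMRM group term, screening a response, linear | 0.44 d | 36% | 30% | 26% |
| MMRM group term, V1 and V3 only, linear | 0.67 d | 59% | 53% | 48% |
| MMRM group term, screening a response, constant | 0.67 d | 67% | 58% | 50% |
| MMRM group term, V1 and V3 only, constant | 1.00 d | 91% | 86% | 82% |
| Two-sample t-test, raw V3 | d | 75% | 75% | 75% |
| Two-sample t-test, change to V3 | d | 61% | 75% | 93% |
| V3 difference adjusted for baseline | d | 79% | 86% | 96% |

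If the effect appears only at V3, the group term has 17–23% (screening a response) or 30–37% (V1 and V3 only).

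**Before/after tests.** Suppose both arms change equally, by c SD, at rho = 0.5. Each arm's paired test has SE sqrt(1/15) = 0.258 and is significant with probability p = 0.19, 0.44 and 0.71 for c = 0.3, 0.5 and 0.7. Exactly one arm is significant with probability 2p(1 − p) = 0.31, 0.49 and 0.41, although the arms do not differ.

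**Normality test.** In 4,000 simulated samples of 15, the Kolmogorov–Smirnov test (with estimated mean and SD) flagged exponential data 44% of the time and moderately skewed lognormal data 26% of the time. It is a weak guide at this sample size.

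**The case against.** The strongest reply is that the article already contains a valid comparison. A two-sample test applied to V3 scores, or to change, estimates the V3 difference without bias in a randomized trial; leaving out baseline costs precision only. That stands. A reader might infer that the fatigue and muscle analyses cannot estimate the week-9 effect at all, and the article does not support that. It would also be misleading to set the lowest MMRM figures alone against the baseline-adjusted ones, because the planned two-sample test lies between.

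Second, the lowest MMRM figures need both a gradual effect and the screening value as a response, and the article states neither. If the response is change at V1 and V3, the SE is sqrt[(2/15)((1 + rho)/2 + 1 − 2 rho)]. At rho = 0.6 this is 0.283, giving 62% under linear build-up and 93% under a constant effect, against 91% for the baseline-adjusted V3 difference. So the V3 contrast is not always the more powerful choice. An average over treatment visits is also a legitimate summary, and the article does not name week 9 as the target. This stands, and it is why the size is given as a range.

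Third, the article is condensed, and the full protocol or analysis plan may add an interaction or covariate. That is possible. But the article does list the model's factors, so this is a stated specification, and the list should be complete enough to show what is estimated.

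Finally, three tempting readings go beyond the text. The article does not say that the before/after tests are run within each arm, that the normality result selects the test, or that significance in one arm only will be read as a treatment effect. The first two are natural readings; the third is a misuse that the article never proposes.

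**Conclusion.** The point holds in limited form. Read as written, the MMRM gives no visit-specific difference. Its group term equals the V3 difference only when the effect is constant from V1 and the pre-treatment value is not a response. In the cases examined it otherwise recovers 0.33 to 0.67 of that difference. The two-sample test remains an unbiased route to the V3 difference, at 75% power on raw scores or 61–93% on change against 79–96% with baseline adjustment. The gain from adjustment over raw scores is therefore 4 to 21 percentage points (79 − 75 to 96 − 75), and over change scores 3 to 18 (96 − 93 to 79 − 61).

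All power figures rest on the assumed 1 SD effect, equal correlations of 0.3 to 0.7 and complete data. No figure in the article is shown to be wrong. Because these are secondary outcomes in a pilot sized by feasibility, the weight is minor to moderate. The lack of a named lead analysis is the part most worth settling before unblinding.

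**What to change.** For each fatigue and muscle score with repeated measurements after baseline, specify an MMRM with treatment, visit, treatment-by-visit and the pre-treatment value as covariate. Name the treatment difference at V3, with its 95% CI, as the lead estimate. For measures taken only once after baseline, use ANCOVA on the pre-treatment value. Where Table 1 schedules differ, as for the body composition test, state which pre-treatment measurement is the covariate.

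Report before/after changes within arms descriptively, as means with confidence intervals and no p-values. Optionally, drop the normality test and keep the Wilcoxon rank-sum test as a fixed sensitivity analysis.

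The cost is analysis-plan wording and one or two degrees of freedom. The pre-treatment and V3 values needed for the fatigue and muscle scores in Table 1 are already scheduled.
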